### Role of the participants and the general public in the study

*What was the research question, the outcome and outcome measures of the study and how were they developed?* A pilot questionnaire to explore the usefulness of an N_2_O acclimatising appointment prior to actual treatment, from the participants’ point of view was carried out in a group of 15 child participants (range: 5–15 years). The outcome of this survey was indecisive with 8 out of 15 children expressing a predilection for commencing treatment without an acclimatising session to N_2_O. This resulted in the formulation of the primary outcome measure of our study on investigating the differences in the participants reported dental anxiety scale in children belonging to the study and control groups.

*What were the preferences and experiences of the participants and their influence in designing the study?* We asked the aforementioned children regarding their feeling in carrying out the completion of the MCDASf (anxiety survey). All the children in this survey mentioned that completing MCDASf was acceptable to them. In addition, we showed and placed the E4 watch on their wrists and asked if they would be happy to wear the watch throughout the treatment. Out of 15 children, 13 were happy with wearing the E4 watch; 2 children found it uncomfortable.

*Involvement of participants in the recruitment to and conduct of the study*. The potential participants will already be patients indicated for N_2_O sedation and are on the DDH sedation list.

### Ethical aspects and approval

This study will be conducted in full conformance with principles of the “Declaration of Helsinki”, Good Clinical Practice, and within the laws and regulations of the UAE/Dubai Healthcare City. Participants (legal guardians and children) who meet the aforementioned inclusion criteria will be enroled in this study. An informed consent (verbal and written) will be provided to the parents/caregivers of the child before the N_2_O sedation and enrolment in the study. Partakers and their parents/guardians will be appropriately informed about the set objectives of the study; each participant will be ensured anonymity. Following data analysis, consolidated results will be published. A signed, informed consent form will be required for participation from the parents/caregivers. The Internal Review Board (IRB) committee of Mohammed Bin Rashid University of Medicine and Health Sciences in (MBRU) in Dubai, UAE have approved the study (Reference: MBRU-IRB-2018-014).

### Dissemination of the study’s results

The detailed results and conclusive outcome(s) of the study will be disseminated through peer-reviewed publication/s, conference presentations and the MBRU web site. Additional events will be conducted by inviting stakeholders and groups of interest in inhalation sedation (such as dental teams including general dental practitioners, dental nurses, paediatric dental specialists and consultants to discuss our findings as it will be relevant to all those who manage children who have dental anxiety generally and those using N_2_O specifically).

### The study’s statistical analysis

We will conduct deep statistical analysis after consideration of the data’s distribution normality, with the appropriate parametric or non-parametric statistical tests using the statistical software SPSS™ 24.0.0 (SPSS^©^ Inc., USA). The utilisation of standard descriptive statistics and quantitative data will be reported; if normally distributed, means and standard deviations shall be used; and if skewed, medians and interquartile ranges will be reported. The score of dental anxiety will be calculated for each participant and test for normality by using the Shapiro–Wilk test. Categorical data will be tested for independency by using Chi-square or Fisher's exact test when appropriate. The difference in the means between the two groups will be tested using either *t*-test or Mann–Whitney test depending on the normality of the data. The comparison of the means of more than two variables will be tested by using ANOVA or Kruskal–Wallis depending on the normality of the measurements. A *p*-value of <0.05 will be considered significant in all tests.

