### Secondary outcomes

The following clinical outcomes will be obtained and considered as indications of a beneficial effect of the acclimatisation N_2_O session:The successful completion of the required dental procedure as measured by reviewing the clinical notes documents obtained from the electronic dental records system.The children’s and parents’ acceptance of the treatment with or without acclimatisation session as measured by guardian/child quantitative questionnaire (see below Table 1a, b).

**Table 1 Tab1:** Parent’s (a) and children’s (b) dental treatment acceptance questionnaire.

(a) Parent’s dental treatment acceptance questionnaire					
Statements	Response				
	Strongly agree	Agree	No opinion	Disagree	Disagree Strongly
The dentist explained very well why my child needed dental treatment.					
I have no concerns about how the laughing gas sedation works.					
I think the laughing gas sedation is doing a good job at helping my child to cope with the treatment					
My child coped well with having the laughing gas sedation.					
The dental team were kind and helpful during my child’s treatment.					

(b) Children’s dental treatment acceptance Questionnaire			
Questions	Response		
	Positive	Neutral	Negative
What do you think about your experience with laughing gas?			
Are you glad to have your tooth fixed/extracted?			
How did we look after you when you had your treatment?			
How friendly were we when you came to see us?			
How well did the dentist explain everything about treating your tooth?			
Was it ok having your tooth fixed/extracted?			

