In addition to the MCDASf, physiological anxiety-related changes will be recorded using E4^®^ wrist bands (see Fig. 3). The wrist band will be placed 5 min before the patient comes into the surgery for treatment and will be taken off 5 min after the completion of treatment. This will enable recording physiological parameters continuously before, during and after the dental treatment. E4^**®**^ wrist bands will provide real-time parameters (Fig. 4) such as EDA also known as GSR, BVP, acceleration, HR, and temperature. E4^**®**^ wrist bands are small, simulate wearing a wristwatch, and we do not anticipate any increase in the children’s anxiety as a result of wearing these wrist bands. The E4^**®**^ wrist band was validated^17^ and approved by the United States Food and Drug Administration as a medical device. It is used in a wide range of research settings with configurations for palmar skin conductance measurement or using gelled electrodes secured under the band. Additional evaluation of behaviour (Table 4) will be documented using the numerical FBRS scores (FBRS: 1–4, where 1 is very uncooperative).^12^ Parents and children will be asked to fill in the survey questionnaire after completion of dental treatment visit to assess their perception and approval (or lack of) of dental treatment with or without an accustoming session (Table 1a, b).

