### Calculation of the study’s sample size

The study is sized to have an 80% power to detect a statistically significant difference in children’s behaviour and anxiety level between the two groups. As there are no previous similar studies, the primary outcome measure is a change in anxiety (a reduction mainly). To our knowledge, no studies had investigated the effect of an acclimatising session of N_2_O on the child’s behaviour to base our sample size calculation on. Our biostatistician used Houpt et al. study in 1996 (effects of nitrous oxide on diazepam sedation of young children) to predict the sample size.^18^ The predicted sample size is 33 participants in each group and to compensate for dropouts a total of 70 participants will be recruited for both groups.

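### The only rule for categorical data ignores category order: it reads onto the acceptance items, and the text leaves open whether it also covers the Frankl score

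*Protocol article*

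**What the plan says.** The section on the study's statistical analysis sets rules by type of data and does not assign the Frankl score or the acceptance items to either of them.

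- Categorical data: "Categorical data will be tested for independency by using Chi-square", with Fisher's exact test as the alternative.
- Two-group comparisons: "The difference in the means between the two groups will be tested using either *t*-test or Mann–Whitney test depending on the normality of the data".
- Threshold: "A *p*-value of <0.05 will be considered significant in all tests".

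The only variable named in that section is the dental anxiety score, for the Shapiro–Wilk test. Ordinal data are not mentioned.

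Two sets of outcomes are ordered categories:

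- **Frankl behaviour rating.** It is listed under Primary outcome, and Table 4 defines four described ranks. Study flow and layout says "Additional evaluation of behaviour (Table 4) will be documented using the numerical FBRS scores", running from 1 to 4.
- **Acceptance of treatment.** This is a secondary outcome, "as measured by guardian/child quantitative questionnaire". Table 1 gives parents five boxes from strong agreement to strong disagreement, and children three boxes (positive, neutral, negative). It assigns no numbers to the boxes and defines no total or mean.

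On size, the article states: "The predicted sample size is 33 participants in each group and to compensate for dropouts a total of 70 participants will be recruited".

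**The concern.** A test of independence treats the levels of a scale as interchangeable labels. The null hypothesis in the article is about improvement in behaviour and reduction in anxiety, which is a shift along the scale. An order-free test spreads its power over every way in which two distributions can differ, including patterns with no meaning as better or worse. With 33 children per arm there is little power to spare.

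The second issue is choice. For the Frankl score an analyst could defend a chi-square test because Table 4 describes categories, or a Mann–Whitney test because the scores are called numerical. The two can give different p-values. For a primary outcome measure that choice should be closed before the data are seen.

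**Working it through.** **The plan's own figure.** The sample size section claims "The study is sized to have an 80% power to detect a statistically significant difference in children’s behaviour and anxiety level between the two groups" with 33 per group. It states no effect size, SD or rates, so 33 cannot be reproduced forwards. Solved backwards at two-sided 5% (sidedness is not stated, so this is assumed): d = (1.960 + 0.842) × √(2/33) = 0.69. The step from 66 to 70 matches about 5% dropout (66/0.95 = 69.5). None of this says which test was assumed for ordered outcomes.

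**Which rule covers which outcome.** The acceptance items are verbal boxes without codes, so the categorical rule is the natural one. Describing the questionnaire as quantitative puts no numbers on the boxes. For Frankl, numerical scores from 1 to 4 point to the t-test/Mann–Whitney rule, while four described ranks permit the categorical one. No text settles it.

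**Power if chi-square is used.** I assumed several control distributions and shifted them by a proportional odds ratio: logit P(Y≤j, study) = logit P(Y≤j, control) − ln OR. For example, Frankl 15/35/35/15% at OR 3 becomes 5.6/19.4/40.4/34.6%. There were 33 per arm, two-sided 5%, and 20,000 simulated trials per scenario.

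- Pearson chi-square: X² = Σ(O − E)²/E on k − 1 df.
- Mann–Whitney with tie correction: z = (W − n(N+1)/2) / √{(n²/12)[(N+1) − Σ(t³−t)/(N(N−1))]}, with n = 33 and N = 66.

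With no effect, rejection rates were 4.0–5.5% for chi-square and 4.7–5.2% for Mann–Whitney. Power in %, chi-square v Mann–Whitney:

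| Control distribution, % | OR 2 | OR 2.5 | OR 3 | OR 3.5 | OR 4 |
|---|---|---|---|---|---|
| Frankl 15/35/35/15 | 21.4 v 33.3 | 35.1 v 51.9 | 49.2 v 67.6 | 60.5 v 78.1 | 70.3 v 85.2 |
| Frankl 5/15/45/35 | 19.0 v 31.5 | 32.3 v 48.8 | 44.5 v 63.3 | 57.1 v 74.4 | 65.4 v 81.6 |
| Frankl 25/35/30/10 | 21.5 v 33.2 | 35.7 v 52.5 | 49.8 v 67.7 | 61.2 v 78.6 | 71.0 v 85.6 |
| Frankl 25/25/25/25 | 22.2 v 34.0 | 36.6 v 52.9 | 50.1 v 67.2 | 61.9 v 78.6 | 71.2 v 85.8 |
| Parent 5/10/15/35/35 | 16.7 v 32.8 | 28.3 v 50.8 | 40.2 v 65.3 | 50.5 v 74.8 | 60.0 v 82.9 |
| Parent 20/20/20/20/20 | 20.1 v 34.7 | 32.6 v 53.6 | 46.4 v 68.6 | 57.1 v 79.0 | 67.1 v 86.5 |
| Child 20/30/50 | 23.0 v 29.3 | 35.8 v 44.9 | 47.4 v 57.6 | 57.6 v 67.9 | 65.2 v 75.4 |
| Child 10/20/70 | 15.3 v 21.5 | 22.4 v 32.0 | 30.7 v 42.7 | 37.0 v 50.3 | 42.2 v 55.8 |

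Smallest and largest losses, in percentage points:

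- Child item: 21.5 − 15.3 = 6.2 to 55.8 − 42.2 = 13.6.
- Frankl: 33.2 − 21.5 = 11.7 to 63.3 − 44.5 = 18.8.
- Parent item: 34.7 − 20.1 = 14.6 to 65.3 − 40.2 = 25.1.

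**Check without category distributions.** A 1-df test with 80% power has noncentrality (1.960 + 0.842)² = 7.85. The same noncentrality gives 71%, 64% and 60% power on 2, 3 and 4 df. For 80% power these need noncentralities of 9.63, 10.90 and 11.94. Scaling 33 by the ratio to 7.85 gives about 41, 46 and 50 per arm.

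**Power for Frankl under the other rule.** Shapiro–Wilk rejected normality in essentially every simulated arm of 33 Frankl scores (2,000 arms for each of two distributions). Mann–Whitney would therefore be selected, and the loss does not arise.

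**Limit.** The losses are for Pearson chi-square. Small expected counts were common (in over 99% of tables for the skewed parent item), so Fisher's test would often be the one used. It also ignores order, but I did not compute its power.

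**The case against.** The strongest reply is that the article never assigns these scales to chi-square. Its categorical rule names no outcome and fits treatment completion well. The authors' own labels, numerical for Frankl and quantitative for the questionnaire, point to the other rule, and that rule already contains Mann–Whitney. Matching outcomes to tests is often left to a fuller document. The simulated shift is proportional odds, a pattern that suits a rank test, and the distributions are invented.

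Much of this stands for Frankl. A reader might infer that the plan contradicts itself on the Frankl score, or that a primary outcome measure has already lost power. The text supports neither: no passage places Frankl under both rules, and the numerical label favours the rule that keeps the order. What remains is an open choice and a conditional loss.

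It stands less well for the acceptance items. The questionnaire is called quantitative, but no score is defined to which a t-test or Mann–Whitney test could be applied. The point also does not rest on something left out for another document: the article does state a rule for categorical data, and that rule suits ordered responses badly.

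The reliance on assumed distributions is a fair limit on the figures. The calculation by degrees of freedom needs no category distribution and points the same way, but it too presumes that the effect lies along the ordered direction.

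**Conclusion.** The concern holds in a limited form. The stated rule for categorical data discards order, there is no rule for ordinal data, and on the natural reading the acceptance items fall under the stated rule. For Frankl the applicable test is unsettled, with the wording leaning towards the test that causes no loss.

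If chi-square is used at 33 per arm, the cost is about 6 to 14 points of power for a three-level item, 12 to 19 for Frankl and 15 to 25 for a five-level item. This rests on assumed category distributions, proportional odds ratios from 2 to 4 and a two-sided 5% level. Losses in a real dataset could lie outside these ranges if the effect is not a steady shift along the scale. The point merits a clarifying sentence; it does not threaten the validity of the trial.

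**What to change.** State in the statistical analysis section that the Frankl score and each parent and child acceptance item are analysed as ordinal, with the groups compared by Mann–Whitney. Optionally add a common odds ratio with 95% CI from a proportional-odds model where cell counts allow, so that the direction and size of the effect are reported. Keep chi-square or Fisher's exact test for binary or nominal data such as completion of treatment.

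The cost is one sentence, and Mann–Whitney is already in the plan. There is a small downside to the optional summary: it adds the proportional-odds assumption and may be unstable when cells are sparse at 33 per arm. For that reason the Mann–Whitney test should carry the inference.

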### Primary outcome

The changes in the child’s behaviour and anxiety levels. The primary outcome measures will be assessed byPhysiologically measurable parameters by using a medical grade wearable device (E4^®^ wrist bands—Empatica Inc., [name]—ISO 13485 Cert. No. 9124.EPTC*)*. These parameters areElectrodermal activity (EDA) also known as Galvanic skin response (GSR),Blood volume pulse (BVP),Heart rate (HR),Surface skin temperature.Dental anxiety scores at baseline before the (acclimatisation session) and after treatment (second session) using the Modified Child Dental Anxiety Scale-face version (MCDASf).^11^Children’s behaviour score will be recorded using the Frankl Behaviour Rating Scale (FBRS).^12^

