**Fig. 1 Fig1:**
[figure not shown]
Flowchart of the study design.

A 1:1 allocation-based block randomisation method will be employed. The method of allocation concealment will be attained by using matching, sealed, serially numbered, non-transparent envelopes that will contain group allocation. The envelopes will be opened in sequence by a non-investigator (dental assistant), only after the envelope has been conclusively dispensed to each partaker and will continue to be anonymous to the clinical team.

At the initial screening visit, the anxiety level will be recorded using MCDASf (Fig. 2) to determine the need for N_2_O sedation and subsequently invite the child and parents to participate in the study. Once enroled, an acclimatising visit will be carried out by a single paediatric dentist who will not be involved in the subsequent treatment of the patients. To be constant, an information script will be organised and rehearsed so that the same preoperative instructions about N_2_O sedation will be delivered to all the children and their parents. The patient’s physiological signs will be recorded using the E4^®^ wrist band (Fig. 3). For the study group only, 15 min of N_2_O sedation will be administered without any dental treatment procedures at the acclimatisation visit.

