**Fig. 3 Fig3:**
[figure not shown]
A child wearing the E4 wrist watch.

Throughout the second visit, the dental treatment for both study and control groups will include administering local anaesthesia and restoration of carious teeth, pulp treatment if needed and/or tooth/teeth extractions. The dental treatment will be carried out by the same paediatric dentist. However, a second paediatric dentist blinded to which group the child belongs to will record the FBRS of children while receiving the treatment under N_2_O sedation.

The MCDASf (see Fig. 2) using the SDCEP endorsed and condensed version of the MCDASf questionnaire,^11^ not including the last two questions on dental sedation and GA, will be used for all anxious children. The MCDASf is a validated tool that had been used to assess dental anxiety.^14–16^

The language of the MCDASf questionnaire will be English or Arabic. The English version was translated into Arabic using the forward and backward translation method. The translation was checked by an independent bilingual expert who resolved concerns and discrepancies. To make sure that the translation was effective, a back-translation to the English language was done by an independent translator who back-translated the questionnaire and discrepancies in the translation version were resolved. The total score range of MCDASf is 6–30. Children with a score ≥19 will be considered to have severe dental anxiety (dental phobia), while those with a score of <19 will be considered to have none to moderate anxiety (Table 2).^7^ The treatment complexity rank score (Table 3) records the medical status classification, based on the patient’s (ASA) classification.^13^

**Table 2 Tab2:** Modified Child Dental Anxiety Scores (MCDAS).

Score	Interpretation
5–10	Minimal anxiety
11–18	Moderate anxiety
≥19	Severe anxiety

**Table 3 Tab3:** Treatment complexity rank score.

Rank	Description	Score
Routine	Polishing, fluoride application, fissure sealants, one-surface Restorations	1
Intermediate	2-surface restorations, extraction of 1 primary tooth, one-quadrant restorative dentistry	2
Complex	Crown preparation, pulp treatment, extraction of multiple primary teeth, multiple-quadrant restorative dentistry, extraction of 1 permanent tooth	3
High complexity	Multiple extractions of permanent teeth, surgical extractions, biopsy. Any treatment considered more complex than above or are multiples of the above	4

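### The arms are compared on anxiety scores without adjusting for the baseline MCDASf recorded on every child; the test stays valid but is less precise than ANCOVA, by an amount that depends on a correlation the article does not give

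*Protocol article*

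**What the plan says.** The statistical analysis section sets out the two-group comparison: "The difference in the means between the two groups will be tested using either" a t-test or a Mann-Whitney test, with normality deciding which. The anxiety score is checked with the Shapiro-Wilk test. No covariate and no adjusted model is mentioned. The same section also names Chi-square or Fisher's exact tests for categorical data, and ANOVA or Kruskal-Wallis for more than two variables, but does not assign tests to outcomes. On significance it says only that a p-"value of <0.05 will be considered significant in all tests".

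The baseline score is available. The Primary outcome section lists "Dental anxiety scores at baseline before the (acclimatisation session) and after treatment (second session"), measured by MCDASf, and the study-flow text says "At the initial screening visit, the anxiety level will be recorded using MCDASf", before the family is invited to take part.

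The outcome is described as a change in two places: "The changes in the child’s behaviour and anxiety levels" under Primary outcome, and "the primary outcome measure is a change in anxiety (a reduction mainly") in the sample size section. The analysis section does not say whether the test is applied to the post-treatment score or to the change.

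**The concern.** The baseline value of an anxiety scale is usually a useful predictor of the later value on the same scale. A two-sample test of the post-treatment score ignores it. A test of the change uses it, but with a fixed coefficient of 1 in place of the coefficient the data support. ANCOVA estimates that coefficient and, apart from a small cost in degrees of freedom, is at least as precise as either.

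Two things are at stake. The first is power: 33 per arm can reliably detect only a large standardised difference, so avoidable variance matters. The second is that the reported result is not settled in advance. It could concern the post-treatment score or the change, and it could be a difference in means or a rank comparison chosen by a normality test on the trial's own data.

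**Working it through.** **Inputs from the article.** 33 per arm analysed and 70 recruited; 1:1 allocation; 80% power; significance level 0.05. Sidedness is not stated, and two-sided is assumed here. The article gives no effect size, no SD and no baseline-to-post correlation.

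**Assumptions.** The correlation r between baseline and post-treatment MCDASf runs from 0.3 to 0.7. The variance is equal at the two times. Differences are in units of the post-treatment SD.

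**The plan's own figure.** The sample size section says "The study is sized to have an 80% power to detect a statistically significant difference", but without an effect size or SD the 33 per arm cannot be reproduced. Solving backwards with the normal approximation, d = (1.960 + 0.842) × √(2/33) = 0.69. The exact t calculation gives 0.70.

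**Variance of the treatment effect**, relative to the post-score test:

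- post-treatment score alone: 1
- change score: 2(1 − r)
- ANCOVA: 1 − r²

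**Precision lost relative to ANCOVA:**

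- post-score test: 1 − (1 − r²) = r²
- change-score test: 1 − (1 − r²)/[2(1 − r)] = 1 − (1 + r)/2 = (1 − r)/2

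**Power** comes from the two-sided t-test with 33 per arm and a true difference of 0.5 SD. The effective standardised difference is 0.5 for the post score, 0.5/√[2(1 − r)] for the change and 0.5/√(1 − r²) for ANCOVA.

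| r (assumed) | Loss, post score | Loss, change score | Power, post score | Power, change score | Power, ANCOVA |
|---|---|---|---|---|---|
| 0.3 | 9% | 35% | 52% | 39% | 55% |
| 0.4 | 16% | 30% | 52% | 45% | 59% |
| 0.5 | 25% | 25% | 52% | 52% | 64% |
| 0.6 | 36% | 20% | 52% | 61% | 71% |
| 0.7 | 49% | 15% | 52% | 73% | 80% |

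Worked line at r = 0.5: the ANCOVA variance is 1 − 0.25 = 0.75 and the effective difference is 0.5/√0.75 = 0.577, which gives 64% power. The difference detectable with 80% power falls from 0.70 to 0.70 × √0.75 = 0.61 SD.

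**Cost of estimating the slope.** With 66 children the ANCOVA variance is inflated by about 1 + 1/(66 − 4) = 1.016. The loss for the post-score test then becomes 1 − 0.91 × 1.016 = 7.5% at r = 0.3, 23.8% at r = 0.5 and 48.2% at r = 0.7. The conclusion does not change.

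**The case against.** The strongest reply is that nothing here is an error. Allocation is randomised 1:1, so the unadjusted test has the right type I error and its standard error already allows for chance imbalance in baseline anxiety. That stands. A reader might infer that imbalance biases the trial, and the documents do not support that reading.

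The second reply is that the baseline may already be in use. The article twice calls the outcome a change, so the test may be meant for change scores, where the baseline enters by subtraction. This also stands, and it is why both comparators are shown. It does not remove the point: the analysis section leaves the choice open, and the change-score test still loses 35% to 15% over the assumed range.

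The third reply is that the size is uncertain. It is tempting to say that a quarter of the precision is thrown away, but that figure is simply r = 0.5, and the article gives no correlation. Because MCDASf is also used to decide who needs sedation, the baseline range may be narrowed and r lowered. That would shrink the loss for a post-score test and enlarge it for a change-score test.

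Three further extensions would go too far:

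- The t-test or Mann-Whitney test is not the only between-group analysis named; the categorical tests could serve the Frankl rating.
- The figures do not carry over to the Frankl rating or the wristband measures. No pre-treatment Frankl score is described, and each wristband measure would need its own baseline and correlation.
- Treatment complexity cannot be assumed to be a usable covariate. The text says "The treatment complexity rank score (Table 3) records the medical status classification", which does not show that it is scored before randomisation, and no evidence is given that it predicts anxiety.

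Finally, an analysis plan that is not shown may contain covariate models. That would answer a complaint about an omission. Here the article states the test, and the stated test is what is questioned.

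**Conclusion.** The point holds for the MCDASf comparison, as avoidable inefficiency together with an unfixed choice of analysis. The stated test is unadjusted, the score it applies to is not identified, and a normality test decides between means and ranks, while a baseline on the same scale is in hand for every child. The size rests wholly on the assumed range of r and on equal variances at the two times. The losses for the two unadjusted tests move in opposite directions as r changes, so anywhere between 0.3 and 0.7 at least one of them loses 25% or more. At the low end the gain over a post-score test is modest (52% to 55% power at 0.5 SD); at the high end it is large (52% to 80%). The change is well worth making, but the plan as written is not invalid.

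**What to change.** In the statistical analysis section, prespecify the MCDASf analysis as ANCOVA of the post-treatment score on arm and baseline MCDASf. Report the adjusted mean difference with its 95% CI, whatever the Shapiro-Wilk test shows. Use a rank-based ANCOVA or a bootstrap interval as a sensitivity analysis, not as a replacement chosen from the data. Age may be added as an optional covariate if this is declared in advance. Leave treatment complexity out unless it is shown to be scored before randomisation. If a gain in precision is quoted, state the assumed correlation and its range, and confine the claim to MCDASf.

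The cost is analysis wording and one degree of freedom (two with age). No extra children, visits or measurements are needed.
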